#### Secondary Outcomes

The analysis of secondary outcome variables will adhere to the same methodology used for the primary outcomes. Changes in continuous variables from baseline to week 8 in BDI-II, BAI, PHQ-15, WHOQOL-BREF, PSWQ, PDSS, and LSAS-SR will be assessed using the same analytical approach, with a significance level set at 5%. To evaluate the differences in measurements before and after the intervention within each group, the Student Paired *t* test or Wilcoxon signed rank test will be used for both primary and secondary outcomes. Additionally, to examine the trend changes over time between the EA-MNS and EA-VNS groups, Repeated Measures ANOVA will be conducted. This analysis will include testing the interaction between the groups and visits to ascertain how differences evolve over time. If the interaction is found to be significant, post hoc tests will be implemented to identify significant differences between the groups at specific time points based on baseline measurements. Furthermore, the binary variables such as loss of diagnosis and complete remission of anxiety disorder, as assessed by HAM-A, will be compared between groups using logistic regression, which will provide odds ratios and 95% CI.

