The evaluation of the treatment group is scheduled to occur at the initial, eighth, and final visits. For the control group, assessments will be conducted in the first, fourth, and eighth weeks. During the initial and final assessments for the treatment group, and the first and eighth weeks for the control group, the following instruments will be administered: Hamilton Anxiety Rating Scale (HAM-A) [20], Beck Anxiety Inventory (BAI) [21], Beck Depression Inventory-II (BDI-II) [22], Patient Health Questionnaire-15 (PHQ-15) [23], World Health Organization Quality of Life Assessment Instrument abbreviated version (WHOQOL-BREF) [24], Leibowitz Social Anxiety Scale-Self Report (LSAS-SR) [25], The Panic Disorder Severity Scale (PDSS) [26], and Penn State Worry Questionnaire (PSWQ) [27]. LSAS-SR will be conducted only for patients with social anxiety disorder, PDSS only for those with panic disorder or agoraphobia, and PSWQ only for those with generalized anxiety disorder. A midpoint evaluation using the HAM-A and BAI will be conducted during the eighth visit for the treatment group or in the fourth week for the control group. The detailed schedules are described in Table 1 and the study flow is presented in Figure 3.

**Table 1 table1:** Timeline of the trial.

Period				Screening (week –1)		Treatment									
						Baseline (week 0)	Midterm						Final (week 8)		
							Weeks 1-4		Week 4		Week 5-8				
Visit						Visit 1^a^	Visit 2-7^b,c^		Visit 8		Visit 9-15		Visit 16		
Consent				✓											
Demographic information				✓											
Medical history				✓		✓	✓		✓		✓		✓		
Physical examination				✓											
Vital signs				✓		✓	✓		✓		✓		✓		
Body weight and height				✓									✓		
Laboratory test^d^				✓											
Pregnancy test^e^				✓											
SCID-5^f^				✓											
C-SSRS^g^				✓									✓		
Inclusion and exclusion criteria				✓											
Randomization						✓									
	Item														
		HAM-A^h^, BAI^i^				✓			✓				✓		
		PHQ-15^j^, BDI-II^k^				✓									
		WHOQOL-BREF^l^				✓							✓		
		PSWQ^m^, PDSS^n^, LSAS-SR^o^				✓							✓		
		EQ^p^, PSS^q^				✓							✓		
Emotional reactivity test						✓							✓		
Check concomitant drugs						✓	✓		✓		✓		✓		
Check adverse effects						✓	✓		✓		✓		✓		
EA-MNS^r^, EA-VNS^s^						✓	✓		✓		✓		✓		
HRV^t^						✓			✓				✓		
Education of visit schedule				✓		✓	✓		✓		✓				

^a^Visit 1 is scheduled to occur within 10 days of screening.

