### Statistical Methods: Definition of the Analysis Set

The analysis sets for evaluating data obtained in this clinical trial are defined as follows: the Full Analysis Set is in accordance with to the intent-to-treat principle, encompassing all participants who met the inclusion and exclusion criteria, were randomly assigned, and for whom baseline measurements and at least 1 postbaseline primary outcome was obtained. The Per Protocol Set (PPS) includes participants from the FAS who have adhered to at least 75% of the total intervention and do not meet any discontinuation or dropout criteria. The Safety Analysis Set (SAS) comprises all participants who have undergone at least one safety assessment following random assignment.

All data, including efficacy outcomes, will be analyzed using the FAS, with the PPS serving as a secondary analysis group for additional analyses. Safety variables will be analyzed using SAS. Continuous data will be presented as means and confidence intervals, while categorical data will be presented as frequencies and percentages (%). If necessary, initial characteristics of participants measured at screening or baseline may be categorized for subgroup analysis.

Unless specifically stated otherwise, all statistical analyses in this study's results will be conducted as 2-sided tests, with a significance level set at 5%. However, for the analysis of the primary outcome, the significance level will be set at 2.5%. Statistical analyses will be performed using SAS software (version 9.4 or higher, SAS Institute).

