### Statistical Methods for Analyzing Efficacy Outcomes

#### Primary Outcomes

The primary outcome analysis will use a mixed-effect model repeated measure (MMRM) approach, including each treatment group and visit time point as fixed factors, with participants as random factors, and accounting for interactions between groups and visit time points. Variables that show statistically significant differences in demographic or sociological characteristics, or other factors potentially influencing anxiety disorders, will be incorporated as fixed factors. Results will be presented with means, 97.5% CIs, and *P* values. In addition, if significant baseline differences exist between groups, an Analysis of Covariance (ANCOVA), adjusted for baseline values as a covariate, will be conducted.

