### Statistical Methods to Handle Missing Data

When using the MMRM for variable analysis, no separate imputation for missing values will be conducted. Conversely, in cases where ANCOVA is used, missing values will be imputed using the Multiple Imputation method.

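### Six of the seven secondary scales have no midpoint value, so the primary MMRM without imputation gives them a near complete-case change comparison, baseline-adjusted only after a significant test

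*Protocol article*

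**What the plan says.** Statistical Methods for Analyzing Efficacy Outcomes, Secondary Outcomes, opens with the rule that "The analysis of secondary outcome variables will adhere to the same methodology used for the primary outcomes". It names the endpoints as "Changes in continuous variables from baseline to week 8 in BDI-II, BAI, PHQ-15, WHOQOL-BREF, PSWQ, PDSS, and LSAS-SR", and fixes method and level for them: "PSWQ, PDSS, and LSAS-SR will be assessed using the same analytical approach, with a significance level set at 5" percent. The primary method is an MMRM "including each treatment group and visit time point as fixed factors, with participants as random factors", plus the group-by-visit interaction. The same section adds an ANCOVA on the baseline value, but only if the groups differ significantly at baseline.

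Statistical Methods to Handle Missing Data states: "When using the MMRM for variable analysis, no separate imputation for missing values will be conducted". Multiple imputation is kept for the ANCOVA.

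On timing, Study Procedure gives the full battery at the start and end of treatment ("and the first and eighth weeks for the control group, the following instruments will be administered"). In between, "A midpoint evaluation using the HAM-A and BAI will be conducted during the eighth visit for the treatment group", or in week 4 for controls. No other scale is named for the midpoint. Table 1, as printed, ticks PHQ-15 and BDI-II at baseline only. LSAS-SR, PDSS and PSWQ are restricted to diagnostic subgroups of unstated size.

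The Full Analysis Set (FAS) takes randomised, eligible participants for whom "baseline measurements and at least 1 postbaseline primary outcome was obtained". Results reports 60 enrolled and 51 who completed the intervention.

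**The concern.** An MMRM without imputation is defensible when earlier post-baseline values of the same outcome inform the later missing ones. HAM-A and BAI meet that condition; the other six scales do not. For them the no-imputation rule keeps its wording but loses its justification.

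The FAS admits a participant on a week-4 HAM-A alone. Such a person counts as analysed, yet has no post-baseline value on the six scales, and a model fitted one scale at a time cannot draw on the week-4 HAM-A or BAI. The only stated route to imputation, and to baseline as a covariate, is a significant baseline difference. That test says nothing about whether week-8 data are missing.

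Textbox 2 lists 7 scales × 3 arm pairs + 2 binary outcomes × 3 pairs + 1 HAM-A comparison = 28 secondary comparisons. Of these, 6 × 3 = 18 concern the six scales. At stake are the precision of those comparisons and, if loss depends on early response, some bias.

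**Working it through.** **Post-baseline values per scale.** By the text: BAI two (week 4, week 8), the other six one each. By Table 1: WHOQOL-BREF, PSWQ, PDSS and LSAS-SR one each, PHQ-15 and BDI-II none. If the table is right, those two scales have no change to week 8 to analyse.

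**What the model becomes.**
- *Change to week 8 as response.* Each participant has one value. Visit has one level, group-by-visit drops out, and the participant effect cannot be separated from the residual. What remains is a comparison of change among those with week 8.
- *Baseline as a visit level.* There are two levels and the model can be fitted; group-by-visit is the difference in change. In a simulated set (2 arms of 20, 3 per arm without week 8), the mixed model on completers gave −0.6694, identical to the completers' change-score difference. On all participants it gave −0.6503, because non-completers' baselines still enter.

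Neither version uses week-4 HAM-A or BAI.

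**Baseline adjustment.** With SD 1 and baseline/week-8 correlation ρ, the variance per person is 2(1−ρ) for change and 1−ρ² for ANCOVA. The SE ratio of ANCOVA to change is √((1+ρ)/2): 0.81 at ρ = 0.3, 0.87 at 0.5, 0.92 at 0.7. With 51/3 = 17 per arm and ρ = 0.5, the change SE is √(2/17) = 0.343, and the ANCOVA SE is about 0.343 × 0.866 = 0.297.

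**Missing data.** The article gives no effect size, SD or power for any scale, so there is no plan figure to reproduce and the rest is assumed. Assumptions: 20 per arm; effect 0.8 SD; correlation 0.5 of baseline with week 4 and with week 8; correlation 0.7 of week-4 HAM-A with the week-8 scale; two-sided 5%; 60 − 51 = 9 participants without week 8, all with week-4 data. The split by arm is not in the text and is also assumed. Simulated power:

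| Losses (control/active) | Change, complete case | ANCOVA, complete case | ANCOVA, week-4 imputation |
|---|---|---|---|
| 3/3, random | 61% | 74% | 75% |
| 5/2, driven by week 4 | 55% | 63% | 73% |
| 7/1, driven by week 4 | 51% | 49% | 71% |

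Separate runs under somewhat different assumed loss mechanisms moved the change-score figures between 49% and 63%, and the imputation figures between about 67% and 76%. Type I error was 0.043–0.055 for the change score and for imputation.

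Bias with week-4-driven loss, in SD:
- change score: 0.03 (5/2) and 0.05–0.08 (7/1), toward the null here because controls are lost more;
- complete-case ANCOVA: 0.07 and 0.12;
- week-4 imputation: about 0.

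A separate simulation had no true effect, 3 lost per arm, loss in the active arm depending on week 4, and week-4/week-8 correlation 0.4–0.8. Bias was 0.00 to −0.06 SD for the change score, −0.03 to −0.09 SD with baseline as a visit level, and about 0 with week-4 data. Under random loss, the SE was 0.333–0.341 for the change score and 0.317–0.334 with week-4 data, about 2–5% smaller.

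**The case against.** A reader might infer that the stated model cannot be fitted to these scales at all. The documents do not support that. The model has no baseline covariate and has a group-by-visit term, which fits baseline being a visit level, and then it runs. Which response is meant is a detail that an article may leave to the full protocol or SAP.

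A reader might also credit the whole power gap to missing-data handling. Under random loss, baseline adjustment takes power from 61% to 74% and imputation adds one point. Imputation matters clearly only if loss follows week-4 status.

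Nor may one assume that week-4 data exist for all nine. The article says only that 51 completed the intervention. It does not say how many of the others reached week 4 or lack week 8, and anyone who left before week 4 is outside the FAS.

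The 20-per-arm figures do not describe PSWQ, PDSS or LSAS-SR, where an imputation model with several predictors could be unstable. PHQ-15 and BDI-II depend on resolving Table 1. Only WHOQOL-BREF fits the calculation without a caveat.

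Finally, analysing each outcome without borrowing from other scales is conventional, these outcomes are secondary, and the Sample Size section frames the trial around feasibility and exploratory analysis.

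All of this limits the size of the point. It does not remove the mismatch: a no-imputation rule tied to repeated measures is applied to scales with one post-baseline value, and covariate adjustment hangs on a significance test.

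**Conclusion.** The point holds, at moderate size and for secondary outcomes only. For the six scales the stated analysis is either exactly a complete-case change-score comparison or close to one. It takes baseline as a covariate only after a significant test, and it leaves unused any week-4 HAM-A and BAI of FAS members without week 8, up to 9 of 60 (15%).

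Under the assumptions above, the change-score analysis has little bias (about 0 to 0.08 SD) but power of about 51–61% for a 0.8 SD effect, against about 67–76% for the alternative. The gain from baseline adjustment under random loss needs only a baseline correlation below 1. The gain from week-4 imputation depends on the loss mechanism, the arm split and how many non-completers have week-4 data, none of which the text gives. The primary HAM-A analysis and the BAI analysis are not affected by this point, since each uses its own week-4 value.

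**What to change.** 1. First reconcile Table 1 with Study Procedure on whether PHQ-15 and BDI-II are collected at week 8.
2. In Secondary Outcomes, keep the MMRM for HAM-A and BAI. For the other six scales, specify ANCOVA of the week-8 score on arm and the same scale's baseline score, whatever any baseline test shows.
3. For scales given to all participants, multiply impute missing week-8 values from arm, baseline, and week-4 HAM-A and BAI.
4. For PSWQ, PDSS and LSAS-SR, use a reduced imputation model, or report the baseline-adjusted complete-case ANCOVA and label it so. If loss follows week-4 status, that analysis can be more biased than the change score (0.07 against 0.03 SD in the 5/2 case).
5. In Statistical Methods to Handle Missing Data, limit the no-imputation rule to outcomes with two post-baseline visits.
6. Report how many FAS members lack week 8, by arm, and how many of them have week-4 data.

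The cost is a few sentences and modest programming, with no new data. Imputation assumes that loss is random given arm, baseline and week 4, which is weaker than what a complete-case change comparison assumes. Data collection has ended and analysis is under way according to Results, so the change needs a date and a statement of whether outcome data by arm had been seen.

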**Primary Outcome**
The primary outcome will be assessed by analyzing changes in the Hamilton Anxiety Rating Scale (HAM-A) scores from baseline to week 8 in two separate comparisons:Between the electroacupuncture-median nerve stimulation (EA-MNS) group and the Usual Care group.Between the electroacupuncture-vagus nerve stimulation (EA-VNS) group and the Usual Care group.Research HypothesisHypothesis 1 [H0 : μ1 = μ2, H1 : μ1 ≠ μ2]μ1: Changes in HAM-A score from baseline to week 8 in the EA-MNS groupμ2: Changes in HAM-A score from baseline to week 8 in the Usual Care groupHypothesis 2 [H0 : μ3 = μ2, H1 : μ3 ≠ μ2]μ2: Changes in HAM-A score from baseline to week 8 in the Usual Care groupμ3: Changes in HAM-A score from baseline to week 8 in the EA-VNS group

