### Blinding

Given the nature of the interventions, it is not feasible to blind participants in this study. However, to preserve the integrity of the study outcomes, assessor blinding will be strictly maintained. Researchers responsible for evaluating the efficacy and safety outcomes will not participate in the administration of interventions or the randomization process.

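### Before-after significance tests within each arm are planned for the primary and secondary outcomes and are not labelled descriptive; they bypass the randomised comparison and invite a misleading contrast between arms

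*Protocol article*

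**What the plan says.** The primary outcome box defines efficacy between arms: it concerns "changes in the Hamilton Anxiety Rating Scale (HAM-A) scores from baseline to week 8 in two separate comparisons", one for each electroacupuncture arm against usual care. Both numbered hypotheses have that form. The analysis section matches it: "The primary outcome analysis will use a mixed-effect model repeated measure (MMRM) approach", with group, visit and their interaction.

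The Secondary Outcomes section of the statistical methods then adds a second kind of test, which compares each arm with its own baseline. A paired t test or its rank-based counterpart is named, and the scope is explicit: "Wilcoxon signed rank test will be used for both primary and secondary outcomes". So the before-after tests are a firm plan and cover HAM-A as well as the secondary scales. The article does not say how their results will be interpreted.

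On missing data, the article states: "When using the MMRM for variable analysis, no separate imputation for missing values will be conducted". It prescribes multiple imputation for ANCOVA and gives no rule for the paired tests.

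**The concern.** A before-after test asks whether an arm changed. It does not ask whether the arm changed more than usual care. People enrolled with an anxiety disorder may improve through natural course and regression to the mean, and a paired test in one arm cannot separate that from an effect of treatment. The concurrent randomised control exists to make that separation, and only the between-arm contrast uses it.

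What is at stake is interpretation. With three small arms, some can cross the significance threshold and others miss it by chance even when all improve equally. If an electroacupuncture arm crosses and usual care does not, the pair of P values looks like evidence of benefit but is not a test of any difference. This trial has two electroacupuncture arms set against one control, so there are two chances for the pattern to appear.

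A second, smaller issue is the population. A paired test needs both the baseline and the week-8 value. The repeated-measures model can keep anyone with a baseline and at least one post-baseline score, which is how the Full Analysis Set is defined. The two sets of results would then probably describe different people.

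**Working it through.** **Figures in the article.** Sample Size gives 20 per group: 3 × 20 = 60, which agrees with the stated total. The general level is 5% two-sided, and the level for the primary outcome is 2.5%; 0.05 / 2 = 0.025 is an even split over the two comparisons. Results reports 51 of 60 completing the intervention: 9 / 60 = 15% did not. The article gives no effect size, standard deviation or power, so there is no planned figure for the within-arm tests to reproduce.

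**Assumptions.**
- The true standardised before-after change d is the same in all three arms, so there is no treatment difference. The article gives no d, so a range is shown.
- n per arm is 20 (all randomised) or 17 (51 / 3 = 17, if losses are spread evenly and completing treatment stands in for having a week-8 score).
- Tests are paired t tests, two-sided at 5%. The signed rank version was not computed separately.

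**Step 1: power in one arm.** The power p comes from the noncentral t distribution with n − 1 degrees of freedom and noncentrality d√n. At d = 0.5 the noncentrality is 0.5 × √17 = 2.06 or 0.5 × √20 = 2.24, giving p = 0.491 or 0.565.

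**Step 2: the misleading pattern.** The arms are independent, so:
- one given electroacupuncture arm significant and control not: p(1 − p)
- at least one of the two significant and control not: (1 − p)[1 − (1 − p)²]

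Worked example, n = 17, d = 0.5: 0.509 × (1 − 0.509²) = 0.509 × 0.741 = 0.377.

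| d | p (n = 17) | at least one EA arm, not control (n = 17) | p (n = 20) | at least one EA arm, not control (n = 20) |
|---|---|---|---|---|
| 0.3 | 0.214 | 0.300 | 0.247 | 0.326 |
| 0.5 | 0.491 | 0.377 | 0.565 | 0.353 |
| 0.8 | 0.872 | 0.126 | 0.924 | 0.076 |
| 1.0 | 0.972 | 0.028 | 0.989 | 0.011 |

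The second formula cannot exceed 0.385, reached at p = 0.423. For one given pair the ceiling is 0.25. With no change at all (d = 0) the result is 0.093 counting changes in either direction, and about 0.05 counting improvements only.

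**Step 3: would 2.5% help?** With n = 17 and each within-arm test at 2.5%, the values at d = 0.3, 0.5, 0.8 and 1.0 are 0.219, 0.379, 0.204 and 0.061. The stricter level lowers the figure for small d and raises it for large d, so it does not cure the problem.

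**Step 4: comparison with between-arm testing.** A simulation of 100,000 trials at n = 17 used a simple between-arm t test of the changes in place of the planned model. It agreed with the step 2 values at d = 0.3, 0.5 and 0.8. The chance that either electroacupuncture-control contrast was falsely significant was about 4.7% at 2.5% each, and about 9% at 5% each. Neither depended on the shared change.

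**The case against.** The strongest reply is that the harm needs a misuse the article does not plan. The hypotheses are between arms, the between-arm model is primary, and the paired tests are given the limited purpose of describing change within a group. Nothing says that P values from different arms will be compared or used to claim efficacy. This stands, and it makes the point one of reporting.

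Several stronger readings are tempting but not supported:
- **That the primary result is compromised.** It is not; the model and its hypotheses are untouched. Nor does the article say that the within-arm P values will appear beside the primary result.
- **That non-completers are dropped.** This is an inference from the absence of a rule. The article assigns efficacy data to the Full Analysis Set, and completing the intervention is not the same as having a week-8 score.
- **That the control arm would remove expectancy.** Under Blinding, "it is not feasible to blind participants in this study", and controls receive no treatment, so expectancy can differ between arms and remain in the between-arm contrast. Only natural course and regression to the mean are controlled.
- **That the choice between t and signed rank lacks a rule.** That detail is commonly left to an analysis plan.
- **That the tests fall outside the stricter level.** The article says only that "for the analysis of the primary outcome, the significance level will be set at 2.5" percent, and does not settle which level applies to a before-after test on that outcome.

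A further reply is that a within-arm confidence interval excluding zero invites the same inference as a P value. That is partly right, and it is why the fix also needs a sentence on interpretation. What survives all of this is that the article commits itself to tests that answer none of its hypotheses and does not label them descriptive, although its own model can supply the within-arm change.

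**Conclusion.** The point holds as a minor one. The planned within-arm tests are a weak choice stated in the text, and their cost is a risk of misleading interpretation.

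With no true difference between arms, 17 to 20 analysed per arm and two-sided 5% tests, at least one electroacupuncture arm is significant while usual care is not in about 30-33% of trials at a shared change of 0.3, 35-38% at 0.5, 8-13% at 0.8 and 1-3% at 1.0. A reader might infer that the pattern is frequent whatever the change. It is not: the figures at 0.5 lie close to the 38.5% ceiling, and the risk nearly vanishes once the shared change is large. The article does not say where in this range the trial lies.

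The result rests on the assumed common change, on even attrition for the n = 17 case and on the paired t version of the test. It applies to scales given to everyone, such as HAM-A. The diagnosis-specific scales have fewer people per arm and were not computed.

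**What to change.** In the Secondary Outcomes section of the statistical methods, replace the paired t and signed rank tests with the within-arm mean change at week 8 and its confidence interval, taken from the planned model. Present these descriptively without P values. Add one sentence stating that efficacy conclusions rest only on the between-arm contrasts; this sentence does most of the work.

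The change removes analyses and needs no new data. Taking the estimates from the model also puts them on the same participants as the between-arm results. The article says that data collection has ended and analysis is under way, so the change should be dated and made before results are reported. The small downside is that readers lose the familiar before-after P values.

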## Methods

Study Design

This study is designed as a randomized, 3-arm assessor-blinded, parallel-group clinical trial, which will be conducted at the Daejeon Korean Medicine Hospital of Daejeon University, Republic of Korea. It aims to evaluate the efficacy and safety of 2 distinct electroacupuncture interventions in the treatment of anxiety disorders, in comparison to usual care. The interventions specifically target to stimulate the median nerve via acupoint PC6 and the vagus nerve via acupoint TF4 (Figures 1 and 2) [16,17]. The control group, constituting usual care, will not receive any treatment.

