**Secondary Outcomes**
The secondary outcomes will be assessed as follows:Changes in HAM-A scores from baseline to week 8 between the EA-MNS group and the EA-VNS group.Evaluation of rates of loss of diagnosis and complete remission of anxiety disorder, as measured by HAM-A scores, from baseline to week 8 between the EA-MNS group and the Usual Care group.Evaluation of rates of loss of diagnosis and complete remission of anxiety disorder, as measured by HAM-A scores, from baseline to week 8 between the EA-VNS group and the Usual Care group.Evaluation of rates of loss of diagnosis and complete remission of anxiety disorder, as measured by HAM-A scores, from baseline to week 8 between the EA-MNS group and the EA-VNS group.Changes in Beck Anxiety Inventory (BAI), Beck Depression Inventory-II (BDI-II), Patient Health Questionnaire-15 (PHQ-15), World Health Organization Quality of Life Assessment Instrument abbreviated version (WHOQOL-BREF), Penn State Worry Questionnaire (PSWQ), Panic Disorder Severity Scale (PDSS), and Leibowitz Social Anxiety Scale-Self Report (LSAS-SR) scores from baseline to week 8 between the EA-MNS group and the Usual Care group.Changes in BAI, BDI-II, PHQ-15, WHOQOL-BREF, PSWQ, PDSS, and LSAS-SR scores from baseline to week 8 between the EA-VNS group and the Usual Care group.Changes in BAI, BDI-II, PHQ-15, WHOQOL-BREF, PSWQ, PDSS, and LSAS-SR scores from baseline to week 8 between the EA-MNS group and the EA-VNS group.

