### Sample Size

Considering the absence of prior clinical trials proving the therapeutic effect of electroacupuncture in anxiety disorders compared to a control group, this study references preliminary research recommending a minimum of 15 participants per group to ensure feasibility and facilitate exploratory analyses [33]. Therefore, to accommodate potential variances and ensure statistical robustness, we plan to enroll 15 participants per group, for a total of 45 participants. However, to enhance statistical rigor and account for potential attrition, the final sample size was adjusted to 20 participants per group, yielding a total of 60 participants.

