### Randomization and Allocation

In this study, participants will be randomly assigned to one of the 3 groups: the EA-VNS group, the EA-MNS group, or the usual care group. Stratified block randomization will be used, using SAS software (version 9.4 or higher, SAS Institute), to ensure an unbiased and equal allocation (1:1:1 ratio) across the groups. The stratification criteria will include the specific type of anxiety disorder diagnosed in each participant, such as panic disorder, agoraphobia, generalized anxiety disorder, social anxiety disorder, and other specified anxiety disorders. This method ensures proportional representation of each anxiety disorder subtype within each study arm, thereby controlling for variability in treatment response based on the type of anxiety disorder. The randomization list in this study will be held by an independent statistician and will not be disclosed to ensure confidentiality. The randomized codes will be placed in opaque, sealed envelopes and stored in a locked cabinet. Randomization envelopes will be opened in the order of participant enrollment to assign each group. The opened envelopes will be stored separately, and the date, time of opening, and the opener’s signature will be recorded on the envelopes.

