## Results

This study was funded in December 2022. The first participant was enrolled on December 15, 2022, and the final participant completed the intervention on November 22, 2024. A total of 60 participants were enrolled, and 51 participants completed the intervention. Data collection was conducted from December 13, 2022, to November 22, 2024. Data analysis is currently underway, and the results are expected to be published in 2025. The CONSORT (Consolidated Standards of Reporting Trials) flowchart depicting the study process is presented in Figure 4.

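### The logistic regression fixed for remission and loss of diagnosis has no rule for an arm with zero events, and at low control rates that result is quite possible with 20 per arm

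*Protocol article*

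**What the plan says.** Textbox 2 of the protocol article lists among the secondary outcomes "Evaluation of rates of loss of diagnosis and complete remission of anxiety disorder, as measured by HAM-A scores, from baseline to week 8", for each of the three pairs of arms. That makes two binary endpoints and six comparisons, four of which involve the control arm. Under Statistical Methods for Analyzing Efficacy Outcomes (Secondary Outcomes), these variables "will be compared between groups using logistic regression, which will provide odds ratios and 95% CI". The promise of an odds ratio and interval is unconditional.

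Under Sample Size, "the final sample size was adjusted to 20 participants per group, yielding a total of 60 participants". Results reports that "A total of 60 participants were enrolled, and 51 participants completed the intervention". Under Study Design, "The control group, constituting usual care, will not receive any treatment". Secondary outcomes are tested two-sided at 5%.

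Small counts are provided for elsewhere. Fisher's exact test is named as an option for safety frequencies, and for baseline tables it comes with an expected-count rule. Neither provision extends to the binary efficacy endpoints.

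**The concern.** Standard logistic regression relies on large-sample theory. When one arm has no events, the likelihood keeps rising as the log odds ratio goes to infinity. The estimate and its standard error diverge together, and their ratio, the Wald statistic, shrinks towards zero. The promised odds ratio and interval then do not exist, and a large observed difference is printed with a P value near 1.

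A control arm of about 20 without study treatment could plausibly have no complete remissions. A zero control count beside many treated remissions is also among the most favourable results for electroacupuncture. So the method may fail on the tables that show the clearest benefit. If a substitute is chosen only after such a table is seen, the choice is no longer prespecified.

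**Working it through.** **Inputs from the article.** n = 20 per arm, allocated 1:1:1 (Sample Size; Randomization and Allocation). There were 51 completers, so 51/3 = 17 per arm if the losses were even. Two-sided alpha is 5%.

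**Assumed inputs.** Event rates, because the article gives no remission rate and no HAM-A cut-off for either endpoint. Maximum-likelihood fitting and Wald inference, because neither is stated. The article gives no figure of its own for these endpoints to reproduce; its sample-size arithmetic (3 × 20 = 60) is right.

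**Step 1: chance of zero control events, (1 − p)^n.**

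| True control rate p | n = 20 | n = 17 |
|---|---|---|
| 2% | 67% | 71% |
| 5% | 36% | 42% |
| 10% | 12% | 17% |
| 15% | 4% | 6% |
| 20% | 1% | 2% |

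**Step 2: one table, control 0/20 versus treated 8/20.**
- Maximum likelihood: the iterations stop at a log odds ratio of about 18.8 with SE about 3,306. So z = 18.8/3,306 = 0.006 and Wald P = 0.995. Stopping earlier or later changes these values, because no maximum exists.
- Fisher's exact test: 2 × C(20,8)/C(40,8) = 2 × 125,970/76,904,685, so P = 0.0033.
- Likelihood ratio: 2 × [(8 ln 0.4 + 12 ln 0.6) − (8 ln 0.2 + 32 ln 0.8)] = 2 × (−13.46 + 20.02) = 13.1, so P = 0.0003.
- Firth: in a 2×2 table the estimate equals adding 0.5 to each cell, so OR = (8.5 × 20.5)/(12.5 × 0.5) = 27.9. The penalised likelihood-ratio P is 0.0011, and the profile-likelihood 95% CI runs from about 3 to 3,700.
- Risk difference: 40 percentage points (Newcombe score 95% CI 15.8 to 61.3).
- The article's rule for baseline tables would call for Fisher's test here. The two event cells each have expected count 8 × 20/40 = 4, so 50% of cells fall below 5, against a threshold of 25%.

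**Step 3: probability of P < 0.05, by enumerating all 2×2 outcomes with 20 per arm** (Wald counted as non-significant when an arm has no events or all events).

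| Control vs treated | Wald | Fisher | Firth | Likelihood ratio |
|---|---|---|---|---|
| 2% vs 40% | 24% | 86% | 93% | 94% |
| 5% vs 40% | 42% | 72% | 82% | 83% |
| 5% vs 50% | 57% | 89% | 94% | 95% |
| 10% vs 40% | 46% | 49% | 61% | 63% |
| 20% vs 40% | 25% | 19% | 27% | 29% |

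With 17 per arm, 5% vs 40% gives Wald 27%, Fisher 61% and Firth 74%.

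**Step 4: type I error with 20 per arm.** Firth: 1.2% at 5% vs 5%, 3.9% at 10% vs 10%, 4.9% at 20% vs 20%. The ordinary likelihood-ratio test reaches 8.5% at 10% vs 10%.

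**The case against.** The strongest reply is that the article says only logistic regression. It does not say ordinary, maximum likelihood or Wald. Firth regression is itself a form of logistic regression, and an analysis plan that is not shown may specify it. That stands as a limit: the failure is conditional on the usual fit. But the sentence promises odds ratios and intervals without condition, and read in the usual way it cannot always deliver them.

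A reader might infer that the odds ratios cannot be estimated in this trial. The documents do not support that. It needs an arm with zero events, and control events are plausible. Entry requires no minimum HAM-A score, and stable antidepressants, benzodiazepines and sleeping pills may be continued. With an unstated cut-off, the control rate cannot be known from the text, and it may differ between the two endpoints.

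A reader might also infer that Wald inference is badly conservative whenever events are few. Against Fisher's test it is not, once no cell is zero. For 1/20 versus 7/20, Wald P is 0.039 and Fisher P is 0.044; for 2/20 versus 8/20 they are 0.040 and 0.065.

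It is also true that the false non-significance belongs to the Wald test, since a likelihood-ratio test from the same model detects 0/20 versus 8/20. This helps only in part. A zero cell still leaves no finite odds ratio, and that test can exceed its nominal 5% level (Step 4).

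Finally, categorical data are to be shown as frequencies and percentages, so 0% versus 40% would be visible to readers. The promised inference would still be missing.

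**Conclusion.** The concern holds in conditional form. Given maximum-likelihood fitting and a zero-event arm, the stated method yields no finite odds ratio and no usable Wald interval, and its Wald P value is meaningless. At a treated rate of 40% with 20 per arm, the chance that an arm has no events (or all events) and Fisher's test is nonetheless significant is 63% at a control rate of 2%, 34% at 5%, 11.5% at 10% and 1% at 20%. The problem is therefore material at control rates of about 10% or below and negligible near 20%. These rates are assumptions, because the article gives none.

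The consequence is confined to secondary outcomes, and mainly to the four comparisons with the control arm. The primary HAM-A analysis is untouched. The change is worth making because it is cheap and removes a choice that would otherwise be made after the counts are known.

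**What to change.** In the Secondary Outcomes analysis paragraph, specify Firth penalised-likelihood logistic regression for loss of diagnosis and complete remission, with penalised likelihood-ratio P values and profile-likelihood 95% CIs. Apply it whatever the counts, so that the method does not depend on the data. For each pairwise comparison, add the risk difference with a score or exact 95% CI. Do not report Wald P values or Wald intervals for these endpoints.

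Results states that data analysis is under way, so the change should be dated, documented and fixed before these comparisons are seen.

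The cost is one sentence and one model option, with no new data. The odds ratio is shrunk slightly towards 1. With a zero cell the interval is finite but very wide (about 3 to 3,700 in the example), which is why the risk difference should stand beside it.
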